## Discussion

Studies assessing catheter malplacement find a high percentage of cases of misplacement. Following head trauma, mass lesions, or in slit ventricles, there is a situation of altered anatomy, rendering catheter placement difficult. For example, the ventricles may be compressed and deviated and therefore difficult to cannulate. Furthermore, if the ventricular catheter is placed in the context of a shunt, high revision rates add to patient morbidity and procedural costs. As there is a need to improve current practices in the placement of ventricular catheters, this VENTRI-GUIDE protocol aims to assess if a portable, easy-to-use, mini-tablet-assisted guide for ventriculostomy can increase the accuracy of ventriculostomy in comparison with the freehand pass technique. Our primary outcome is the rate of correct placements of the ventricular catheter, measured using a three-point grading scale for the outcome of each ventriculostomy.

### Factors influencing ventricular catheter placement

There are anatomical, technical, and individual patient- and surgeon-related aspects to consider when placing a ventricular catheter, in particular, ventricular size and choroid plexus distance. Preoperative ventricle size is significant in its relation to the accuracy of catheter placement
[1], which is most relevant in pediatric patients
[27]. Larger ventricles are more likely to have optimally placed catheters, which decreases the risk of proximal obstruction, and hence increases shunt survival. Interestingly, a recent study by Wilson *et al*. in an adult study population (170 patients, mean age 56 years), which is probably comparable to our supposed study group, did not show a correlation of ventricular size by freehand technique (measured as bifrontal ventricular span or by the Evans ratio) with risk of inaccurate placement
[7]. Also the distance to the choroid plexus is described as a factor contributing to catheter occlusion. Ventricular size and choroid plexus distance are related to the first episode of shunt failure, particularly in the pediatric population, because the ventricle size is smaller and the choroid plexus is larger in the pediatric population
[28].

Obstruction, the main cause for shunt failure, may be due to blockage by the choroid plexus, ventricular debris or glial tissue growing into its lumen, or due to reduction in size of the drained ventricle. A retrospective series considering 90 adult and pediatric patients with 116 shunt failures identified as main cause for shunt failure proximal catheter obstruction (38%), followed by infection (29%)
[6]. Mechanical obstruction can be avoided by inserting a sufficiently long catheter with its tip just anterior to the foramen of Monro
[12]. The length, determined in a previous study from the CT scan scout film of the patient, was half of the distance between the external auditory meatus and the midpoint of the coronal suture of the skull, studied in 175 patients, with good results
[12]. Also, Wan *et al*. identified catheter length as a relevant factor in avoiding obstruction. In contrast to their expectations they found, after correcting for age and approach, that a larger catheter (greater than 8.5 cm) was better placed than a shorter catheter
[1]. Finally, the cause of the hydrocephalus is related to the survival of the ventricular catheter, with a higher risk in hemorrhagic ventricles or with ventriculitis. Gender, American Society of Anesthesiologists (ASA) Physical Status classification class, emergency, use of prophylactic antibiotic agents, and duration of surgery were not related to shunt failures in a pediatric population with 90% use of a ventriculo-peritoneal shunt
[5].

### Surgical technique

The classical freehand technique uses anatomical landmarks such as the inner canthus and external auditory meatus. The catheter is placed in the anterior horn of the lateral ventricle through a burr hole just anterior to the coronal suture in the mid-pupillary line (approximately 11 cm above the nasion and 3 cm from the midline). It is associated with difficulty in gaining optimum insertion angle and catheter length with better success rates in experienced surgeons. Optimal trajectories for a frontal approach were in the mean 42° in the sagittal plane and 30° in the coronal plane
[5].

The surgical technique using the frontal burr hole as in the present study has the shortest intracerebral route, with more consistent anatomical landmarks
[1]. Others prefer the parietal approach, as the atrium is usually the most dilated part of the lateral ventricle
[5], proposed for patients with expected relevant reduction of ventricular size after shunting
[29]. The frontal and parietal burr holes are associated with better placement compared to occipital burr holes
[1]. In the present protocol, a uniform frontal approach has been chosen.

For difficult implantation situations and/or inexperienced neurosurgeons, other techniques have been described to reduce the rate of malplacements and related complications. Frameless neuronavigational stereotaxy
[4], conventional stereotactic, and robotic-image guidance techniques
[30] (n = 17 patients) used for small or slit ventricles have demonstrated accurate placement of ventricular catheters, however, in relatively small patient groups. Intracranial neuroendoscopy is another alternative in selected cases
[17]. Also real-time ultrasound-assisted catheter placement is used in older children, with the disadvantage of needing a larger burr hole of 1.5 to 2 cm
[15]. There are some disadvantages of these sophisticated methods, such as the prolongation of operative time and dependence on expensive, and sometimes complicated technologies
[18, 31]. Nevertheless, the complication rate might be reduced. In a recent study by our group on the accuracy of ventricular catheter placement using anatomic landmarks versus neuronavigation or XperCT-laser guidance, ventricles were hit in 69.2% of catheter insertions using anatomical landmarks (non-assisted), as compared to 82.3% with the use of guidance (neuronavigation or XperCT guidance, *P* = 0.043)
[23]. The placements that were non-assisted were significantly more likely to be extraventricular than those using XperCT (odds ratio: 3.73; 95% confidence interval: 1.24 to 11.19; *P* = 0.019). Attempts with non-assisted placement were more likely to result in an unsafe trajectory compared to those using neuronavigation (odds ratio: 3.16; 95% confidence interval: 1.27 to 7.84; *P* = 0.013). However, there was no difference in final intraventricular placement comparing XperCT guidance placement compared to the neuronavigation placement method (odds ratio: 1.44; 95% confidence interval: 0.55 to 3.78; *P* = 0.46).

### Limitations

Simply monitoring of patients and tracking within a study will already improve performance in most cases, and attention to catheter placement will likely have a similar effect
[19]. In addition, this trial is structured to detect a rather large difference in ventricular misplacements. We are seeking an approximate 15% change, from 35 to 20% hit rate, something which may be very difficult to achieve.

A key limitation is the expected to be an imbalance of surgical skill and/or a learning curve. The surgeons who use the freehand technique will be more experienced using the freehand technique than the mini-tablet-assisted method because they will have performed more procedures using freehand, and we may underestimate the effect size of the guide-assisted method.

In addition, we feel that a learning curve is present, but small because of the similarity between the two procedures. Nonetheless, this limitation is common to surgical randomized controlled trials and will be minimized as best as possible within the limitations of our resources, mostly by doing frequent teaching sessions prior to the opening of the trial. The clinical diagnosis might have an impact on the rate of misplacements with highest rates for suboptimal placements in trauma patients with a midline shift on a CT scan
[21], an effect reducible using randomization, as in the present study.

In conclusion, we have developed a protocol to evaluate if an easy-to-use, portable, image-guided system could reduce the need for multiple passes and improve the rate of accurate catheter placement compared to the standard freehand technique. In contrast with earlier studies, this study is prospective, controlled, and randomized. Considering the high revision rates for patients, especially with small ventricular sizes, the guided technique may lead to better outcome and may be cost-effective. Since the outcome of catheter placement is assessed using an established grading system for catheter tip location post-surgery as the primary endpoint, this study will provide an answer for whether an increase of accuracy for ventriculostomy can be reached in patients with guided ventriculostomy.

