The guiding instrument consists of a base with three pins to be rigidly placed on the bone surface over the burr hole. A semicircular guide rod (Aesculap AG, Tuttlingen, Germany is mounted to the base in which an angle scale is engraved. Within the guide rod, a tube can be individually adjusted in one orientation at different angulations with a range from -60° to 60°. Different tubes are designed with inner diameters of 2, 2.5, and 3 mm in order to guide catheters at different sizes. At the respective angle adjustment, the tube is fixed to the guide rod by a mounting screw. The base is opened at one side to enable the view or insertion of any instrument towards the lower opening of the tube. The guiding tool is positioned parallel to the midline along the engraved linear markings on the base of the instrument. Thereby, a rectangular insertion towards the sagittal convexity and an individual insertion angle towards the coronal tangent at the entry point can be established via the tube.

After opening the dura, once the appropriate trajectory is chosen, a ventricular catheter is inserted according to the pre-calculated insertion angle (for a detailed description see Thomale *et al*.
[20]). After receiving tactile feedback from entering the ventricle, the stylet is removedCerebrospinal fluid (CSF) drainage ensures that the ventricular catheter is correctly in place. Catheters deemed to be suboptimally placed are repositioned when necessary. We rely on length markings on the ventricular catheter and, when possible, flow through the distal catheter to ensure the catheter has not been moved after fixation to the skin and is continuing to provide a conduit for CSF. The remainder of any following shunt procedure or connection to an Ommaya reservoir will be performed using standard techniques.

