### Data documentation

The following parameters will be recorded and used to demonstrate successful randomization and the presence of even baseline groups (Table 
1):Age (years);Gender (nominal male/female);Glasgow Coma Score on admission (ordinal, 1 to 15-point scale);Cause of hydrocephalus/slit ventricles Preoperative ventricle size - width (millimeters);Preoperative ventricle size - using the frontal occipital horn ratio (FOHR; millimeters);Preoperative ventricle size - and the width of the lateral ventricle in the coronal plane between the medial wall of the corpus callosum and the septum;Preoperative ventricle size - using the Evans ratio (bifrontal ventricular span, the ratio of maximum width of the frontal horns to the maximum width of the inner table of the cranium; millimeters),Episode of care (nominal, *de novo*/revision) Time from symptom onset to *admissi*on (hours);Time from symptom onset to randomization (hours);Time from symptom onset to EVD (external ventricular drainage placement (hours);Duration of hospital stay (days);Duration of EVD being in place (days);Presence of CSF infection during the first 14 days, as defined by modified clinical diagnostic criteria for device-associated meningitis (treatment required on either positive culture, or elevated cell count, red cell:white cell ratio, increased lactate, and/or decreased glucose (nominal, yes/no) [22].The EVD catheter placed for ventriculoperitoneal shunting (nominal, yes/no).Any associated endoscopic procedure, for example, third ventriculostomy (freetext);Neurosurgical experience of primary operator (years).

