### Reporting and statistical analysis

The reporting of this trial will conform to the reporting guidelines outlined in the Consolidated Standards of Reporting Trials (CONSORT) for non-pharmacological interventions statement of 2010
[25]. The statistical analysis will be by the intention-to-treat principle. The occurrence of the primary outcome (number and frequency of correct ventriculostomy) will be compared between the two randomization groups. The secondary outcome analyses will compare the above-described variables between randomization groups. Subgroup analyses will be performed to evaluate whether other parameters such as age, ventricle size, diagnosis, or experience of the surgeon may influence the results. Data are presented as mean and standard deviation or as median with 25/75 percentiles. Stata version 11.2 StataCorp. 2013. *Stata Statistical Software*, College Station, Texas, United States) will be used for all analyses.

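### Midline shift, which the protocol itself cites as the highest-risk setting for misplacement, is absent from the listed baseline variables and the named analysis factors

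*Protocol article*

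**What the plan says.** The protocol article touches on this in five places.

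- **Limitations.** Diagnosis may affect misplacement, "with highest rates for suboptimal placements in trauma patients with a midline shift on a CT scan". The stated protection is randomisation: "an effect reducible using randomization, as in the present study".
- **Randomization.** Permuted blocks are used. No stratification factor is stated.
- **Data documentation.** The list has an explicit purpose: "The following parameters will be recorded and used to demonstrate successful randomization and the presence of even baseline groups". It includes the cause of hydrocephalus or slit ventricles, operator experience and four ventricle-size items: a width, the frontal occipital horn ratio, the Evans ratio and "the width of the lateral ventricle in the coronal plane between the medial wall of the corpus callosum and the septum". Midline shift is not on it.
- **Reporting and statistical analysis.** Subgroup analyses will ask whether "other parameters such as age, ventricle size, diagnosis, or experience of the surgeon may influence the results". The list is open, but shift is not named.
- **Discussion, opening paragraph.** Head trauma, mass lesions and slit ventricles are given as altered anatomy, for example because "the ventricles may be compressed and deviated and therefore difficult to cannulate".

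**The concern.** The article names one setting as carrying the highest rate of suboptimal placement and relies on randomisation to deal with it. It then prints a long, specific list for demonstrating balance that leaves this factor out. The four size items describe how large the ventricles are. None describes how far they are displaced sideways.

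Shift could also bear on the comparison itself. Freehand placement aims by external landmarks, which do not move with the ventricles. In the guided arm, "The guiding tool is positioned parallel to the midline along the engraved linear markings on the base of the instrument", and the angle is taken from the patient's own coronal section. The two techniques may therefore respond differently to displacement. Table 1 grades an ipsilateral frontal horn differently from a contralateral one, so lateral displacement is relevant to the endpoint.

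At stake are the ability to show balance on a predictor that the protocol names, some precision in the primary estimate, and a prespecified rather than post hoc look at displaced anatomy.

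**Working it through.** **Step 1. The plan's own figure.** Inputs from Sample size analysis: 31% misses freehand, relative risk 0.5 (so 15.5% guided), 80% power, read as two-sided 5%. The mean rate is 0.2325.

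n per arm = [1.96·√(2·0.2325·0.7675) + 0.8416·√(0.31·0.69 + 0.155·0.845)]² / 0.155² = (1.1709 + 0.4942)² / 0.024025 = 115.4, so 116.

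The plan states 118, which gives 80.9% power. It reproduces to within two patients. No stated figure concerns midline shift, so everything below rests on assumptions.

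**Step 2. Chance imbalance.** The SD of the between-arm difference in prevalence p is √(2p(1−p)/118). Assume that 10 to 25% of patients have a shift and miss at 50 to 60%, with 31% overall. The miss rate without shift is then (31 − p × rate with shift)/(1 − p).

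| Prevalence | Miss rate with shift | Miss rate without | Gap (points) | 2-SD imbalance (points) | Movement of risk difference (points) |
|---|---|---|---|---|---|
| 10% | 50% | 28.9% | 21.1 | 7.8 | 1.6 |
| 10% | 60% | 27.8% | 32.2 | 7.8 | 2.5 |
| 25% | 50% | 24.7% | 25.3 | 11.3 | 2.9 |
| 25% | 60% | 21.3% | 38.7 | 11.3 | 4.4 |

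With a flat 20-point gap and 1.96 SD, prevalences of 10, 20 and 30% give imbalances of 7.7, 10.2 and 11.7 points and movements of 1.5, 2.0 and 2.3 points. Over both sets the range is about 1.5 to 4.4 points, or 10 to 28% of the planned 15.5.

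The table applies the freehand gap to both arms. If the guide halves misses in every patient, the average gap is (1 + 0.5)/2 = 0.75 of that, and the movements shrink in proportion.

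**Step 3. Comparison with the sampling error already allowed for.** The SE of the risk difference is √[(0.31·0.69 + 0.155·0.845)/118] = 5.4 points, giving a 95% half-width of 1.96 × 5.4 = 10.6 points. A 2-SD movement of 1.5 to 4.4 points is one component of that error, not an addition to it.

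**Step 4. What adjustment could gain.** The share of outcome variance explained is p(1−p)·gap²/(0.31·0.69). Row 1 gives 0.09·0.211²/0.2139 = 2%, and row 4 gives 0.1875·0.387²/0.2139 = 13%. As a rough guide, the SE falls from 5.4 to between 5.4·√0.98 = 5.35 and 5.4·√0.87 = 5.04 points.

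**Step 5. What a subgroup analysis could show.** Prevalences of 10, 20 and 30% leave about 12, 24 and 35 patients with shift per arm. The Step 1 formula, solved for power at 31% versus 15.5%, gives 14%, 24% and 34%. For an interaction test, assume misses of 50% versus 25% with shift and a relative risk of 0.5 in the rest. Power is then about 8%, 12% and 19%.

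**The case against.** The case against is substantial, and most of it stands.

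- **Validity.** A reader might infer that an imbalance in shift would bias the primary result unseen. The documents do not support that. Randomisation makes the comparison unbiased, and the test and interval allow for chance imbalance in unmeasured factors (Step 3).
- **Recoverability.** A reader might infer that the trial could never check, adjust for or test shift. That goes too far. Each indication is CT-proven, clinical data are available from electronic patient files, and the subgroup list is open. Shift could be read later. What would be lost is prespecification.
- **Coverage.** A reader might infer that the anatomy motivating the trial goes unrecorded. The Discussion does not name midline shift, and the Limitations sentence is about diagnosis. Cause is recorded and diagnosis is a planned subgroup factor. Slit ventricles are covered by ventricle size, also a planned factor. Cause remains an imperfect stand-in, since it does not show which trauma or mass-lesion patients have a shift.
- **The size measures.** It is tempting to say that the protocol collects variables it knows to be uninformative. The null result it cites covers only bifrontal span and the Evans ratio, and the same section also cites evidence that ventricle size matters.
- **Condensed article.** The full case report form and any analysis plan are not shown and may hold the item. If so, confirmation is enough. The point survives because the article prints a specific list with a stated purpose, and that list omits a predictor the article names.

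**Conclusion.** The point holds as a cheap improvement of low severity. The Limitations section and the Data documentation list do not fit together: the one relies on randomisation for a named risk factor, and the other, meant to demonstrate the result of randomisation, leaves that factor out. No figure in the plan is wrong, and the primary comparison is valid without the change.

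The size is modest and illustrative. The 1.5 to 4.4 points rest on assumed prevalences of 10 to 30% and an assumed excess miss rate of about 20 to 39 points, neither of which the documents give. The gain lies in a visible balance check and somewhat better precision. It does not lie in a firm answer for displaced ventricles, which a trial of 236 patients could not give even with the variable recorded.

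**What to change.** 1. In Data documentation, add preoperative midline shift (mm), read from the existing preoperative CT without knowledge of arm.
2. In Reporting and statistical analysis, prespecify it as a covariate in an adjusted analysis of catheter-tip placement. Report the adjusted result as a risk difference and relative risk standardised over the trial population, so that it matches the effect measures already planned.
3. Label any treatment-by-shift analysis exploratory, test it as an interaction, and state that power is low.
4. In Limitations, point to the recorded variable, so that the reliance on randomisation can be checked.

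The cost is one measurement per existing CT and one case report form field. Sample size, imaging and randomisation do not change. If the full case report form already holds the item, only steps 2 to 4 remain.

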## Trial status

The planned study start date is 1 March 2015. The estimated study duration will be three years.

## Abbreviations

CT: Computed tomography.
